# Assessing and Improving the Care of Patients With Heart Failure in Ghana: Protocol for a Prospective Observational Study and the Ghana Heart Initiative-Heart Failure Registry

**DOI:** 10.2196/52616

**Published:** 2024-04-08

**Keywords:** clinical, cross-sectional, epidemiology, Ghana, heart failure, heart, management, medium-term, monitoring, mortality, outcome, patient data, prevention, protocol, teaching, treatment

## Abstract

**Background:**

Heart failure (HF) is a leading cause of morbidity and mortality globally, with a high disease burden. The prevalence of HF in Ghana is increasing rapidly, but epidemiological profiles, treatment patterns, and survival data are scarce. The national capacity to diagnose and manage HF appropriately is also limited. To address the growing epidemic of HF, it is crucial to recognize the epidemiological characteristics and medium-term outcomes of HF in Ghana and improve the capability to identify and manage HF promptly and effectively at all levels of care.

**Objective:**

This study aims to determine the epidemiological characteristics and medium-term HF outcomes in Ghana.

**Methods:**

We conducted a prospective, multicenter, multilevel cross-sectional observational study of patients with HF from January to December 2023. Approximately 5000 patients presenting with HF to 9 hospitals, including teaching, regional, and municipal hospitals, will be recruited and evaluated according to a standardized protocol, including the use of an echocardiogram and an N-terminal pro-brain natriuretic peptide (NT-proBNP) test. Guideline-directed medical treatment of HF will be initiated for 6 months, and the medium-term outcomes of interventions, including rehospitalization and mortality, will be assessed. Patient data will be collated into a HF registry for continuous assessment and monitoring.

**Results:**

This intervention will generate the necessary information on the etiology of HF, clinical presentations, the diagnostic yield of various tools, and management outcomes. In addition, it will build the necessary capacity and support for HF management in Ghana. As of July 30, 2023, the training and onboarding of all 9 centers had been completed. Preliminary analyses will be conducted by the end of the second quarter of 2024, and results are expected to be publicly available by the middle of 2024.

**Conclusions:**

This study will provide the necessary data on HF, which will inform decisions on the prevention and management of HF and form the basis for future research.

**Trial Registration:**

ISRCTN Registry (United Kingdom) ISRCTN18216214; https:www.isrctn.com/ISRCTN18216214

**International Registered Report Identifier (IRRID):**

DERR1-10.2196/52616

## Introduction

### Overview

Heart failure (HF) is a costly, multifaceted, and life-threatening syndrome characterized by significant morbidity and mortality. Globally, HF affects 64 million people, with a prevalence of 1%-2% of adults in the general population and an estimated incidence of 1-20 cases per 1000 person-years [1].

Sub-Saharan Africa (SSA) has no population-based data; however, in-hospital prevalence ranges from 9.4% to 42.5% [2,3]. HF in SSA mainly affects young people and middle-aged individuals, occurring in people aged between 36 and 62.4 years [4]. It poses a substantial disease burden, with high mortality, rehospitalization rates, and health care costs, primarily attributable to readmissions and prolonged hospitalization periods of 11-13 days [3,5,6].

HF contributes significantly to Ghana’s cardiovascular disease burden, with a worse prognosis and a more malignant course [7,8]. It is a leading cause of death among Ghanaian adults; yet, there is a paucity of data on the epidemiological profiles, treatment patterns, and survival rates of patients with HF in Ghana [9-11]. Single-center studies indicate a high prevalence of HF in Ghana [7,8,12].

The diagnosis of HF in most patients is primarily based on clinical manifestations due to the limited availability of diagnostic equipment. Ghana has few cardiologists, who are mainly located in tertiary hospitals [13]. In addition, there is a lack of HF education and training for physicians and nonphysician health workers. While HF management teams or multidisciplinary teams for HF management are the gold standard model for the delivery of care, these teams are nonexistent in Ghana, and most health facilities lack resources for long-term patient follow-up, such as diagnostic equipment, dedicated HF clinics, and protocols [14-17].

A national network of heart failure management teams (NNHFMT) will be established as part of the Ghana Heart Initiative’s efforts to improve cardiovascular disease care in Ghana to help mitigate the burden of HF. The NNHFMT is tasked with building the capacity of both secondary and tertiary levels of care to promptly and effectively identify and manage HF by creating heart failure management teams (HFMTs) and establishing a national registry for HF and HF clinics that will be integrated with routine clinical services to provide long-term follow-up and care. The establishment of HF clinics and a national registry will fill a significant gap in HF care and research by providing the most recent epidemiological, management patterns, and medium-term outcomes data on HF.

### Objectives

The primary objective of this study is to determine the epidemiological characteristics and medium-term outcomes of HF in Ghana by outlining the epidemiological and clinical characteristics of patients with HF in Ghana, identifying the underlying causes, evaluating the medium-term outcomes of HF in Ghana, and identifying the factors that predict hospitalization and mortality in patients with HF in Ghana. This study also aims to build capacity in the care of patients with HF and form the basis for a national registry for HF in Ghana.

## Methods

### Overview

An NNHFMT consisting of physicians, nurses, and researchers from 9 collaborating hospitals in Ghana was constituted to achieve the study objectives, with each institutional HFMT led by a cardiologist, 2 supporting cardiologists or physicians, and 2 nurses. The HFMTs will establish HF clinics and integrate them into the routine services of their hospitals; recruit patients with HF and manage them per guidelines and algorithm; and create awareness and train other personnel in the 9 centers on the diagnosis and management of HF. These institutions include 5 teaching hospitals, 3 regional hospitals, and 1 municipal hospital. They include the Korle-Bu Teaching Hospital (KBTH), Komfo Anokye Teaching Hospital (KATH), Tamale Teaching Hospital (TTH), Ho Teaching Hospital (HTH), Cape Coast Teaching Hospital (CCTH), Bono Regional Hospital, Presbyterian Hospital-Agogo, Kumasi South Hospital, and the Effia Nkwanta Regional Hospital (Figure 1) [18].

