### Study Design

This is a prospective, multicenter, and multilevel observational study of patients with HF. Patients presenting with HF will be recruited and evaluated according to a standardized protocol. Guideline-directed treatment for HF will then be prescribed after the diagnosis has been confirmed. The study will conduct a serum N-terminal pro-brain natriuretic peptide (NT-proBNP) and transthoracic echocardiogram for all participants for free, while the cost of treatment and other investigations will be borne by study participants as in routine care. Patients will be followed up prospectively for 6 months to determine the medium-term outcomes of interventions (Figure 2).

Patients will be recruited through the collaborating institutions’ emergency rooms, admission wards, and established HF clinics from January to December 2023. The HFMTs of the 2 leading teaching hospitals in Ghana, KBTH and KATH, will be trained using a facilitators’ training manual, which will be developed from current international HF guidelines. KBTH and KATH will then provide mentorship and training to the other collaborating hospitals. The HFMT of KBTH will train members of the HFMTs from the TTH, HTH, and Effia-Nkwanta Regional Hospital, while the HFMT of KATH will also train the HFMTs of CCTH, Bono Regional Hospital, Presbyterian Hospital-Agogo, and Kumasi South Hospital. The study will begin in the KBTH and KATH in January 2023, while the other 7 sites will begin recruitment in July 2023, and all areas will end enrollment in December 2023.

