### Treatment of HF

A modified treatment algorithm adopted from the 2021 European Society of Cardiology Guidelines for treating acute and chronic HF (Figure 4) will be used in the treatment of patients [19].

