### Ethical Considerations

Ethical approval has been obtained from the Ethical and Institutional Review Boards of Korle-Bu Teaching Hospital (STC/IRB/000150/2022), Cape Coast Teaching Hospital (CCTHERC/EC/2023/019), Tamale Teaching Hospital (TTH/R&D/SR/229), Ho Teaching Hospital (HTH-REC (30) FC_2023), and Komfo Anokye Teaching Hospital (KATH IRB/AP/166/22). All participants will be informed about the study, its objectives, and the data collection methods. Consent will be obtained from participants who agree to be part of the study and are assured of strict confidentiality and anonymity. Participants will also be informed that participation in the study is entirely voluntary, and all the services they receive at the clinic will continue as usual whether they decide to participate or not. A unique study number will be assigned to each participant, and the collected data will be deidentified. Only the assigned unique number will be used on study documents related to participants. Participants will also be informed that they can withdraw from the study at any time they choose without consequences.

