## Discussion

### Overview

HF is one of the leading causes of hospital admissions in developing countries and is predicted to experience the most rapid growth worldwide [2,7,31,32]. This prospective study will answer many clinical questions about HF in Ghana. First, this study will address a notable data scarcity in HF care and research in Ghana by establishing a national HF registry, thus creating a vehicle for the accrual of large, comprehensive, and contemporary data encompassing the sociodemographic, clinical profiles, causes of HF, management of HF, and determinants of outcomes such as mortality and hospitalizations of patients with HF in Ghana. In addition, a national HF registry will also provide a good opportunity to evaluate adherence to current guidelines and response to treatment among patients with HF in Ghana.

Clinical registries play a crucial role in gathering real-world data, essential for developing evidence for best clinical practice, measuring outcomes, providing feedback to clinicians, and enhancing the quality of care [1,33]. HF registries, like the Swedish Heart Failure Registry, have played a significant role in advancing knowledge and improving the management of HF. Established in 2000 and implemented nationwide in Sweden by 2003, this registry has yielded valuable research outcomes that have led to notable improvements in the understanding and care of patients with HF and under-treatment detection [1]. The NAtional TUnisian REgistry of Heart Failure (NATURE-HF) contributed valuable data that have the potential to enhance the treatment and overall prognosis of individuals with HF in North Africa [34]. Valuable data were also derived from the Abeokuta Heart Failure Clinical Registry of patients presenting with acute HF in Abeokuta, Nigeria, including acute HF presenting at a relatively younger age, commoner in men, and associated with severe symptoms [35].

While the acquisition of realistic data will address the data gap, this pragmatic study will provide capacity building for the management of HF by enhancing the skills and knowledge of health care providers in diagnosing and treating HF and making diagnostic equipment, including echocardiography, electrocardiograms, and point-of-care NT-proBNP devices, available to participating hospitals. Furthermore, participating institutions’ HFMTs and HF clinics will broaden the prospect for specialist HF care and long-term follow-up in their regions.

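### Six-month results obtained under project-trained teams and a project treatment algorithm are framed as outcomes of heart failure in Ghana, in a study called both observational and an intervention

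*Protocol article*

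**What the plan says.** **Care set by the project.** The Methods Overview describes teams assembled for the study at 9 hospitals, which will set up heart failure clinics and "recruit patients with HF and manage them per guidelines and algorithm". Under Study Design, the two lead hospitals' teams are trained from a manual and then train the other seven sites. The same section states: "Guideline-directed treatment for HF will then be prescribed after the diagnosis has been confirmed". Treatment of HF says that a modified algorithm "will be used in the treatment of patients". The abstract's Methods paragraph adds: "Guideline-directed medical treatment of HF will be initiated for 6 months, and the medium-term outcomes of interventions, including rehospitalization and mortality, will be assessed". The Results paragraphs of the abstract and of the main text both refer to the project as an intervention.

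**Care described as observed.** Study Design opens by labelling the study observational. Strengths and Limitations repeats the label and uses it only to disclaim causal conclusions.

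**What the results are said to represent.** The primary objective is the epidemiology and medium-term outcomes of heart failure in Ghana. The Introduction expects the clinics and registry to fill a national gap by "providing the most recent epidemiological, management patterns, and medium-term outcomes data on HF". The Discussion sees the registry as a chance to "evaluate adherence to current guidelines and response to treatment among patients with HF in Ghana". The Introduction also says that heart failure teams are absent from the country and that most facilities lack dedicated clinics and protocols.

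**The concern.** An outcome estimate needs a stated population and a stated setting of care. Here the setting of care is new: the teams, their training, the clinics and the algorithm all arrive with the project, and NT-proBNP and echocardiography are free to participants. The population named in the objective is patients with heart failure in Ghana, most of whom, on the article's own account, have no access to such care.

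If the results are reported under the objective as worded, six-month mortality and rehospitalization from the programme could be taken as the prognosis of heart failure under ordinary Ghanaian care. Treatment recorded after enrolment could likewise be taken as the national practice that the Introduction says is undocumented. Calling the same project both an intervention and an observational study leaves the reader unsure whether team care is the background being observed or the thing being evaluated.

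**Working it through.** The point depends on no figure in the plan, so the check is a comparison of statements.

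1. **Who decides treatment after enrolment?** Methods Overview, Study Design and Treatment of HF agree: the project's teams, following guidelines and the modified algorithm, once the diagnosis is confirmed.

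2. **Did this care exist before?** The Introduction says that such teams did not exist and that most facilities lacked clinics and protocols. Study Design starts recruitment in January 2023 at the two lead hospitals and in July 2023 at the other seven. The table of timelines marks the establishment of clinics in the same two months. No pre-programme period is therefore built into the enrolled cohort at any site.

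3. **Where is it delivered?** At 5 teaching, 3 regional and 1 municipal hospital (5 + 3 + 1 = 9).

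4. **What is the design called?** Study Design contains both descriptions in one paragraph: it opens with the observational label and closes by speaking of the outcomes of interventions.

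5. **Is the claim limited anywhere to this care?** The Objectives do not limit it. Strengths and Limitations addresses association versus causality, but not whether the results carry over to care without such a team.

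6. **Can existing practice be recovered?** Only from treatment before the team prescribes. Data Collection lists questionnaires and record review, which could hold prior medicines, but does not name them. Recruitment takes in patients already diagnosed and patients with suspected heart failure, and Study Design adds emergency rooms and wards as entry points. A newly diagnosed patient would not be expected to be on heart failure treatment. Medicines at presentation therefore inform on practice only among those previously diagnosed.

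7. **Can the size be computed?** No. The article gives no background level of guideline-directed treatment, no mortality or rehospitalization rate under existing care, and no expected rate under the programme. The precision of ±1% in Study Population concerns six-month mortality and hospitalization. It is a statement about sampling error and does not cover a gap between programme care and existing practice.

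**The case against.** The strongest reply has four parts.

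**The observational label is legitimate.** There is no allocation and no comparator, and guideline care given under a protocol can be observed. This stands. The label is not wrong in itself; the trouble is that it sits beside the intervention wording while the results carry no limit on the setting of care.

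**The usual-care wording does not contradict the algorithm.** A reader might infer a direct contradiction from Ethical Considerations, where patients are told that "all the services they receive at the clinic will continue as usual whether they decide to participate or not". The documents do not support that reading. The sentence is a consent assurance about voluntary participation, and it fits a clinic that has become part of routine service. The routine-care phrase in Study Design concerns who pays. The point does not rest on either passage.

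**Management patterns and adherence are not planned analyses.** They appear in the Introduction and the Discussion as expected benefits of the clinics and registry, and are absent from Objectives and from Data Handling and Analysis. This also stands, so the point on them is conditional on their being reported. Six-month outcomes, however, are in the primary objective.

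**Nothing is hidden.** The article says openly that trained teams, clinics and guideline treatment are part of the project, so an attentive reader can see the setting. That is true of the Methods, but the objective and the limitations are what will be carried into the conclusions, and neither says it.

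**Conclusion.** The concern holds as a matter of what the results can be said to represent. Six-month mortality and rehospitalization, and any adherence or treatment-pattern output based on prescribing after enrolment, describe care under this programme at 9 hospitals. The wording of the objective is broader than that, and the limitations section does not narrow it.

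The size of any difference from existing practice cannot be derived from the document. A reader might infer that adherence will be high by construction, or put a number on the overstatement. Neither is supported. Participants pay for their treatment, so uptake will also reflect affordability. The Discussion itself doubts that guidelines fit settings with limited resources, and the algorithm figure is captioned for reduced and mildly reduced ejection fraction only. Any percentage-point gap would be the difference between two assumed values, and it should not be set beside the ±1%, which is not about adherence.

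The conclusion rests on taking the article at its word that the teams are new and that they manage enrolled patients by the algorithm. It takes no view on which treatment rule is right.

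**What to change.** - Reconcile the observational and intervention wording across the abstract, Study Design, Results and Strengths and Limitations, so that the status of team care is stated once and consistently.
- Restate the outcome objective as six-month outcomes under heart failure management team care at the 9 participating hospitals, and add the same limit to Strengths and Limitations.
- If management patterns or guideline adherence are reported, give two separate results: medicines at first presentation, before the team prescribes, among patients with previously diagnosed heart failure; and treatment prescribed after enrolment, labelled as programme care. The first is possible only if the questionnaires and record review in Data Collection capture prior medicines and whether heart failure was already diagnosed. Confirm this before promising the result.

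The cost is a narrower claim for the six-month results and a little extra analysis. Recruitment, sample size and treatment are unchanged, and no treatment rule is proposed.

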**Figure 1 figure1:**
[figure not shown]
Map of Ghana showing the location of collaborating centers. Source: Ghana Statistical Service, 2020.

### Study Design

This is a prospective, multicenter, and multilevel observational study of patients with HF. Patients presenting with HF will be recruited and evaluated according to a standardized protocol. Guideline-directed treatment for HF will then be prescribed after the diagnosis has been confirmed. The study will conduct a serum N-terminal pro-brain natriuretic peptide (NT-proBNP) and transthoracic echocardiogram for all participants for free, while the cost of treatment and other investigations will be borne by study participants as in routine care. Patients will be followed up prospectively for 6 months to determine the medium-term outcomes of interventions (Figure 2).

Patients will be recruited through the collaborating institutions’ emergency rooms, admission wards, and established HF clinics from January to December 2023. The HFMTs of the 2 leading teaching hospitals in Ghana, KBTH and KATH, will be trained using a facilitators’ training manual, which will be developed from current international HF guidelines. KBTH and KATH will then provide mentorship and training to the other collaborating hospitals. The HFMT of KBTH will train members of the HFMTs from the TTH, HTH, and Effia-Nkwanta Regional Hospital, while the HFMT of KATH will also train the HFMTs of CCTH, Bono Regional Hospital, Presbyterian Hospital-Agogo, and Kumasi South Hospital. The study will begin in the KBTH and KATH in January 2023, while the other 7 sites will begin recruitment in July 2023, and all areas will end enrollment in December 2023.

**Figure 2 figure2:**
[figure not shown]
Chart outlining study design.

### Study Population

Study participants will include patients aged 13 years or older who present with HF in the collaborating hospitals and consent to participate in the study. Patients with a life expectancy less than the expected duration of the registry due to non-HF comorbidities will be excluded.

Based on our estimation of a sample size of 5000 participants, we would be able to determine the mortality and hospitalization rate at 6 months with a 95% CI and a precision of ±1%. Each participating center will recruit 556 participants.

### Recruitment of Study Participants

Participants will be recruited through the various departments or units of the collaborating institutions. All patients diagnosed with HF or suspected of having HF will be referred to the HFMTs for evaluation and enrollment. A total of 2 sensitization workshops will be organized at collaborating institutions during the study period: 1 before participants’ enrollment and 1 midway through participant recruitment.

